### Conservative fluid management

Outpatient/emergency department: All these participants will be considered adherent.

Inpatient: Adherence is defined by the administration of < 110% of maintenance fluids calculated according to the Holliday–Segar formula [38] during the period of time when the participant was in the fluid administration phase of the pathway (defined as per hyperhydration). Thus, adherence to the conservative fluid management pathway is defined as the administration of fluids at or below the following threshold: 100% maintenance fluids × 1.1 × number of hours the participant was in the fluid administration phase. Boluses will be included in the quantification of total fluids. Exact monitoring and recording of oral fluid intake are logistically prohibitive and will not be included in the fluid calculation.

The management of patients who receive > 110% of maintenance intravenous fluids will be classified as nonadherent. However, all patients will be included in ITT analyses regardless of the volume of fluids administered; secondary analyses will include a per protocol adherence analysis.

### Relevant concomitant care permitted or prohibited during the trial {11d}

We will permit the concomitant administration of all medications, supplements, complementary and alternative therapies, treatments, and/or procedures as deemed necessary by the responsible treating physicians. The study will not supply or recommend any specific rescue medication. As part of the overall site education strategies, we will discourage the use of antibiotics, opioids, antimotility agents, and nephrotoxic agents such as non-steroidal anti-inflammatory drugs. We will discourage the use of hypotonic intravenous fluids and will recommend balanced solutions instead of 0.9% saline. However, as this is a pragmatic embedded clinical trial, the treating clinicians, with input from patients and guardians will be responsible to make all treatment decisions.

All relevant data will be extracted daily during chart reviews to enable clarification and confirmation in real-time, if required, and will include concomitant medications administered during the patient’s current illness and any antibiotics taken in the past 14 days. By collecting this information and incorporating it into study analyses, we will be able to identify the independent effects of administered concomitant medications and study interventions.

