## Interventions

### Explanation for the choice of comparators {6b}

Both treatment pathways reflect widely accepted, albeit usually implemented in a non-standardized manner, treatment approaches used in North American Institutions. As it is unknown which approach is most beneficial, there is equipoise. Both pathways have been reviewed and accepted by critical stakeholders at each institution (including emergency medicine, nephrology, gastroenterology, infectious diseases and hospital medicine) as reasonable and appropriate care options. Embedding protocolized management of either clinical approach (i.e., hyperhydration or conservative fluid management) may lead to improvements over current practice, reducing undesirable outcomes by avoiding dehydration, use of antibiotics or antimotility-agents, and by facilitating close follow up and early recognition of complications.

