## Assignment of interventions: blinding

### Who will be blinded {17a}

This will be an unblinded study. Assessment of the primary endpoint, MAKE30, is objective and unlikely to be influenced by lack of blinding. Participating sites will be provided with their allocated pathway that will be embedded into clinical care, thus blinding is not feasible.

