## Statistical methods

### Statistical methods for primary and secondary outcomes {20a}

Baseline characteristics of subjects will be summarized by intervention group. Counts and proportions will be used for categorical variables and means, standard deviations, medians, and quartiles will be used for numeric variables.

We will adhere to the ITT principle. The primary outcome, the MAKE30, will be compared between children allocated to hyperhydration vs. those allocated to conservative fluid management. We will use logistic regression with generalized estimating equation (GEE) methods to account for clustering at the site level. Fixed model terms will include treatment effect and period effect. Other baseline terms in the model will be age (as a continuous variable), serum creatinine, and hematocrit. These variables have been associated with adverse kidney outcomes in this population. The superiority test of null treatment effect will be carried out at the 0.05 level. Parameter estimates and 95% confidence intervals will be provided for all model terms. Carry-over effect will not be present in our crossover design in the traditional sense as patients themselves, and therefore, their outcomes will only be subject to one type of treatment. The only possible “carryover” effect would be a lack of adherence to the new treatment protocol after the crossover at the site level. We will monitor this closely and its potential effect which would be to reduce power.

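### The protocol promises independent effects of concomitant medications and of the pathways, but the medications are not randomised and the design cannot deliver that

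*Protocol article*

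**What the plan says.** Under Relevant concomitant care {11d}, the protocol permits all medications and other therapies "as deemed necessary by the responsible treating physicians" and adds that "the treating clinicians, with input from patients and guardians will be responsible to make all treatment decisions". Charts are reviewed daily, and the extracted data "will include concomitant medications administered during" the current illness "and any antibiotics taken in the past 14 days". From collecting these data and putting them into the analyses, the section concludes that "we will be able to identify the independent effects of administered concomitant medications and study interventions".

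Under Who will be blinded {17a}: "This will be an unblinded study". The primary model, under Statistical methods {20a}, has treatment and period, and then: "Other baseline terms in the model will be age (as a continuous variable), serum creatinine, and hematocrit". It has no medication term. The intervention descriptions {11a} admit every hyperhydration child. In the conservative arm, admission is left to the clinical team unless microangiopathy is present, when it is recommended.

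**The concern.** The sentence in {11d} is a causal claim without qualification, and it covers two different things.

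- **Medication effects.** No medication is randomised. If sicker children receive more drugs and are also more likely to reach MAKE30, a drug that does nothing will appear harmful. The protocol's own Introduction faults earlier fluid studies for unmeasured confounding and for the difficulty of separating cause from association. Medication comparisons inside this trial have the same weakness.
- **Pathway effect.** A medication given after time 0 may depend both on the arm and on how ill the child becomes. Conditioning on it compares children who are no longer alike by randomisation. For example, if admission raises use, medicated hyperhydration children are on average less severely ill than medicated conservative-arm children. The same holds among the unmedicated, so hyperhydration looks protective. If the pathway lowers use, the sign reverses.

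The drugs in question include antibiotics, opioids, antimotility agents and NSAIDs, which the protocol already discourages. A confounded coefficient reported from a phase III trial could be read as confirmation of harm, or set against the valid ITT result. The section on additional analyses {20b} requires results for exploratory outcomes to be identified as exploratory; {11d} attaches no such label to this claim.

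**Working it through.** **The plan's own figure.** The claim has no figure attached. The nearest is the power statement, checked only to confirm the trial's dimensions. Inputs from Sample size: 26 sites, 1040 children (520 per arm), 10% vs 5%, ICC 0.106, alpha 0.05 (two-sided assumed).

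- Effective n per arm for a cluster crossover = n/(1 − ICC) = 520/0.894 = 581.7.
- Power = Φ{[0.05 − 1.96·√(2·0.075·0.925/581.7)] / √[(0.10·0.90 + 0.05·0.95)/581.7]} = Φ{(0.05 − 0.0303)/0.0154} = Φ(1.283) = 90.0%. The plan states 90%.
- The same formula with 400 per arm gives 81.2%. The plan states 81%.

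A direct simulation of the 26-site case gave 86.5%. Power is not the issue here, and nothing below uses it.

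**Model for the check.** T is pathway, S is severity (SD 1), M is medication and Y is MAKE30, for 26 sites × 2 periods × 20 children:

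- logit P(Y) = a + b·S + site effect, with no T term and no M term, so both true odds ratios are 1;
- logit P(M) = c + g·S + t·T.

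The analysis model has T and period, with or without M. The quantities b, g, t and the rate of medication use are **assumptions**; the protocol gives none of them.

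**Set 1.** Severity unmeasured, MAKE30 10%, medication use 30%, latent ICC 0.106, site-robust standard errors, b = 1.0 or 1.5.

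| g | t | Medication OR | Medication significant | Pathway OR with M | Pathway significant, without M | Pathway significant, with M |
|---|---|---|---|---|---|---|
| 0 | 0, ±1 | 0.98-1.00 | 5.4-6.1% | 1.00-1.01 | 5.8-7.9% | 6.1-8.0% |
| 0.5-1.5 | 0 | 1.51-3.77 | 49-100% | 1.00 | 4.9-7.6% | 5.5-7.5% |
| 0.5-1.5 | +1 | 1.51-3.78 | 49-100% | 0.78-0.92 | 4.5-8.5% | 9.1-24.1% |
| 0.5-1.5 | −1 | 1.51-3.78 | 49-100% | 1.09-1.26 | 5.7-8.5% | 9.7-22.5% |

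**Set 2.** A measured baseline covariate carries part of the severity; b = 1.5, t critical value 2.064, 2000 trials each.

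- Half of the severity variance measured, g = 1.0 or 1.5: medication OR 1.78-2.24, significant in 68-90%. Pathway significant in 10.0-10.5% when t = 1 (5.0-5.8% without M) and 4.9% when t = 0.
- All of the severity measured: medication significant in 4.8-5.4%, pathway in 5.4-6.0%. No bias.

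**Set 3.** Baseline covariate correlated 0.3 or 0.6 with severity, b = 1.5 and g = 1.0 or 1.5 unless stated, 400 trials each. The Monte Carlo standard error near 5% is √(0.05·0.95/400) = 1.1 points.

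- Strong arm difference (use 18-19% conservative, 35-46% hyperhydration): pathway significant in 15-43% with M and 5-9% without, OR 0.69-0.85; medication significant in 89-100%.
- Modest arm difference (log-OR 0.3, about 17-20% vs 21-24%): pathway 7-10% with M and 5.5-8.7% without, OR 0.92-0.96.
- No arm difference: pathway 5.5-8.5% with or without M, OR 0.98-1.01.
- Weak severity links (g = 0.5, b = 1.0, correlation 0.6): medication significant in 21-24%.

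**Reading.** The false medication effect needs only that use follows severity the model has not captured. The pathway bias needs, in addition, that the arm shifts use or recording.

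**The case against.** The sentence sits in a concomitant-care section and names no estimator. None of the statistical sections contains a medication term, and {20a} refers further detail to an analysis plan that is not shown. The simulations therefore test one simple implementation with invented inputs. This stands as a limit on the numbers. It does not rescue the sentence, which asserts a conclusion that treatment given by clinical judgement cannot guarantee, whatever model is chosen.

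Four stronger readings are tempting, and the documents do not support them.

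- **That the arms are shown to differ in medication use.** The comparator section {6b} speaks of "reducing undesirable outcomes by avoiding dehydration, use of antibiotics or antimotility-agents, and by facilitating close follow up", but it credits this to protocolised management under either approach, relative to current practice. The discouragement of particular drugs in {11d} also applies to both arms. The only support is the difference in admission, which is plausible but unquantified. Poorer recording for outpatients is likewise an inference: the body of the schedule of activities is not shown, and its notes mention contact by phone, text or e-mail.
- **That all the medications follow the start of the pathway.** The antibiotic history reaches back 14 days, and a note to the schedule of activities covers treatment before eligibility. For these drugs the only problem is confounding.
- **That the bias would be a spurious benefit of hyperhydration.** The sign follows the assumed direction of the arm difference.
- **That the primary result is compromised.** It is not; the primary model adjusts for baseline variables only.

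It is also fair that medications after time 0 should not be barred from every model. The as-treated analysis of fluid volume announced in the Discussion may have good reason to adjust for them.

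**Conclusion.** The claim to identify independent effects should not stand. For medications, confounding by indication is built into the design. With no true effect, false significance ran from 21-24% under weak assumed severity links to 100% under strong ones. It vanished only when severity was fully captured or did not drive use.

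For the pathway, the bias is conditional. It needs a medication given after time 0, an arm difference in its use or recording, and incompletely captured severity. Rejection stayed at the level seen without the medication term when there was no arm difference, reached about 9-24% with a log-OR of ±1, and 43% under the strongest links tried. That medication use follows severity is inferred from clinicians prescribing according to need, and every rate rests on assumed inputs. With the primary ITT analysis untouched, this is a correction that should be made to a secondary claim and is no threat to the main result.

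**What to change.** In {11d}, and in the analysis plan to match:

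- Delete the claim to identify independent effects.
- State that medications started after time 0 will be tabulated by arm and will not be covariates in models estimating the randomised (ITT) pathway effect on primary or secondary outcomes.
- State that medications taken before time 0, such as the antibiotics of the preceding 14 days, may serve as baseline covariates.
- Label any medication-outcome association, and any as-treated or mediation analysis that uses medications started after time 0, as exploratory and non-randomised, without causal wording.

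This takes one or two sentences in each document and no new data. The trial gives up a stated conclusion about concomitant drugs, but one that its design cannot support.

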### Provisions for post-trial care {30}

As study participation involves only data and biospecimen collection, there are no anticipated harms associated with study participation. All participants will receive standard of care as per their hospital’s routine care of children with STEC infection.

### Outcomes {12}

#### Primary outcome: MAKE30 (major adverse kidney events by 30 days)

Because clinical research evaluating the prevention and treatment of AKI has been hampered by the unclear relationship between acute changes in kidney function and longer-term outcomes, the National Institute of Diabetes and Digestive and Kidney Diseases (NIDDK) [40] workgroup on Clinical Trials in AKI recently recommended the use of the MAKE30, a composite endpoint, for phase III trials related to AKI [25]. It is defined by:Death ORProvision of dialysis ORSustained loss of kidney function (at 30 days) reflected by a 100% [41] increase (i.e., doubling) of serum creatinine from baseline

This outcome will be classified following the completion of data extraction and the 30-day follow-up assessment (time 0, as defined above, is used to calculate the 30-day interval). It will be adjudicated based on laboratory values, chart documentation, and 30-day laboratory results. As baseline creatinine values are rarely available for children, all participants will be assigned a value which will be calculated employing a standardized baseline glomerular filtration rate (GFR = 120 ml/min/1.73m^2^) [42].

#### Outcome justification

The rationale for selection of the MAKE30 as the primary outcome is twofold: (1) the kidneys are the major target organ through which STEC infections cause adverse outcomes and (2) the kidneys are the organ system most likely to benefit from the proposed intervention. Several prior cohort studies demonstrated that RRT use, a component of the MAKE30, is reduced with the use of aggressive intravascular fluid administration in STEC-infected children [18–20]. In addition, the MAKE30 is a widely used and easily assigned composite endpoint of AKI as it includes variables related to kidney prognosis and is based on objective endpoints (i.e., death, provision of RRT, sustained loss of kidney function at 30 days) and thus is unlikely to be influenced by knowledge of study group allocation. The MAKE30 outcome has been used in several recent high profile acute care trials focusing on AKI [41, 43]. In addition, pediatric sepsis survivors who experience the MAKE30 outcome have a three- to fivefold higher rate of developing chronic kidney disease [44].

#### Secondary outcomes

These will focus on quantifying other measures of efficacy and safety. They have been selected to provide supportive information about the effect of volume expansion on the primary outcome and the natural history of disease (see Table 1).

**Table 1 Tab1:** Outcomes

Outcome measures			
Type	**Name**	**Time frame**	**Brief descriptions**
Primary	Major adverse kidney events to 30 days (MAKE30)	30 days	MAKE30 is defined as: 1) Death due to any cause censored at 30 days after enrollment OR 2) Provision of RRT, any modality, within 30 days of trial enrollment OR 3) Sustained loss of kidney function (100% increase of serum creatinine from baseline at 30 ± 7 days) Baseline serum creatinine: eGFR (120 ml/min/1.73m^2^) will be used to impute an estimated baseline value. This estimate will be applied to all patients as most patients will not have a baseline value from within the 3 months preceding study 30-day serum creatinine: these will only be required for participants with an elevated value at the time of fluid pathway termination who do not receive RRT
Secondary	Significant extrarenal complications of HUS (life-threatening)	30 days	a. Neurologic i. Seizures requiring anticonvulsant therapy ii. Coma: depressed mental state requiring mechanical ventilation for airway protection and/or ventilatory support iii. Thrombotic or hemorrhagic stroke confirmed by neuroimaging b. Cardiac i. Myocardial infarction: elevated troponin and electrocardiographic features of myocardial ischemia with cardiologist assignment of myocardial infarction ii. Myocarditis: elevated troponin along with cardiologist assigned diagnosis of myocarditis iii. Myocardial dysfunction: reduced ejection fraction requiring inotropic agents iv. Cardiopulmonary arrest requiring cardiopulmonary resuscitation and/or extracorporeal membrane oxygenation v. Arrhythmias requiring electrical or chemical cardioversion or pharmacological anti-arrhythmic therapy c. Respiratory i. Respiratory failure requiring invasive mechanical ventilation (i.e., via an endotracheal tube) ii. Pleural effusions requiring thoracostomy or thoracentesis d. Gastrointestinal i. Hyperglycemia requiring insulin therapy at time of hospital discharge ii. Bowel obstruction/perforation requiring surgical repair iii. Intussusception requiring reduction iv. Acute cholecystitis requiring decompression v. Pancreatitis with lipase > 3.0 × upper limit of normal (ULN) for age vi. Hepatitis/liver failure when any one of the following biochemical criteria are met: bilirubin (when other liver functions are in the normal range) > 3.0 × ULN; bilirubin (when accompanied by any increase in other liver function test) > 1.75 × ULN; AST, ALT, and GGT > 8 × ULN vii. Ascites requiring paracentesis a. Infectious complications i. Bacteremia with or without hypotension requiring inotropic support ii. Peritonitis with or without hypotension requiring inotropic support
Secondary	Development of HUS of any severity (i.e., including those who do not meet the MAKE30 endpoint among those without HUS at randomization)	30 days	HUS is defined as [19]: 1) Anemia (hematocrit level < 30%) AND 2) Thrombocytopenia (platelet count < 150 × 10^3^/mm^3^) AND 3) AKI (serum creatinine concentration > upper limit of reference range for age)

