## Abstract

**Background:**

Shiga toxin-producing *E. coli* (STEC) infections affect children and adults worldwide, and treatment remain solely supportive. Up to 15–20% of children infected by high-risk STEC (i.e., *E. coli* that produce Shiga toxin 2) develop hemolytic anemia, thrombocytopenia, and kidney failure (i.e., hemolytic uremic syndrome (HUS)), over half of whom require acute dialysis and 3% die. Although no therapy is widely accepted as being able to prevent the development of HUS and its complications, several observational studies suggest that intravascular volume expansion (hyperhydration) may prevent end organ damage. A randomized trial is needed to confirm or refute this hypothesis.

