**Fig. 4 Fig4:**
[figure not shown]
The conservative fluid management pathway leaves the decision to admit the child to the discretion of the clinical care team. If microangiopathy is present admission is encouraged. For inpatients and outpatients, laboratory monitoring should be performed a minimum of every 24 h until discharge criteria are met. If intravenous fluids are administered, the maximum rate is 100% of maintenance and the target is euvolemia and maintaining weight gain below < 5%. The pathway should be discontinued once the same criteria are achieved as for the hyperhydration pathway (Fig. 3)

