#### End-of-fluid protocol criteria

The pathways will end when the at-risk window for developing HUS, or worsening HUS if present, has passed and this time point is defined by:Platelet count is > 50 × 10^9^/L (in the absence of transfusion) ANDPlatelets have increased by ≥ 5%* (in the absence of transfusion) since preceding test ANDAbsence of diarrhea (loose or watery stool) × 24 h AND ≥ 5 days since the onset of diarrhea

*If >10 days since the onset of diarrhea, up to a 5% decrease in platelet count since preceding test is acceptable.

In addition, the fluid pathways should no longer be followed in children meeting any of the following criteria:Decision to initiate RRTAnuria for ≥ 12 hHypoxemia requiring supplemental oxygenWeight gain > 15%Hypertensive emergency

If *any of* these criteria are met, the treatment pathway will not resume once they are resolved; care tailored to each patient should be provided as directed by the responsible physician.

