### Participant timeline {13} (Table 2)

**Table 2 Tab2:**
[figure not shown]
Schedule of activities

^1^Stool testing performed to confirm presence of STEC. If a patient was discharged and found to have a positive STEC result, they may be called back if allocated to a hyperhydration site. Patients meeting criteria will be approached for consent

^2^Collection of data pertaining to treatment administered prior to eligibility being established and consent being obtained, if applicable

^3^Phone, text, or e-mail

^4^Can occur as late as day 37

^5^Zip code

^6^Blood type, screen, & culture (if febrile)

^7^Electrolytes, creatinine, urea nitrogen, lactate dehydrogenase; Incl. method, if performed at an alternate laboratory from the enrollment center

^8^Creatinine labs will be required for those with elevated creatinine at hospital discharge who do not receive RRT or, if out-patient, at the time of study intervention phase discontinuation

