### Sample size

#### Target study sample size

We estimate the overall study sample size required is 1040. The number to be screened will likely be 25% higher given that some children will be ineligible, and some will decline consent. Preliminary data indicate that the primary outcome event rate in the conservative fluid management arm will be approximately 10%. The study will be powered to detect a 5% absolute reduction (risk ratio 0.5) in the rate of MAKE30 in the hyperhydration arm. Using a conservative estimate of 5–15 subjects per year per site, we used simulated data (R software) to generate a power table (Table 3) for a 20- or 26-site cluster-crossover design under varying underlying intra-class correlation (ICC) values. The table shows that power is not highly dependent upon ICC and that 20 and 26 sites are required for 80% and 90% power, respectively, at the ICC estimated from preliminary data (i.e., 0.106) [16]. We expect very low levels of missing data, as participants with elevated creatinine values at the time of discharge will have laboratory follow-up as part of their standard clinical care. Patients who deteriorate and develop the MAKE30 outcome will be readily identified. Thus, the impact of loss to follow-up on power is expected to be minimal.

**Table 3 Tab3:** Power calculations for the primary outcome

Intraclass correlation coefficient	20 cites (approx. 800 subjects)	26 sites (approx. 1040 subjects)
0.05	82%	89%
0.106^a^	81%	90%
0.15	85%	94%

^a^Estimate from preliminary data [16]

The anticipated HUS rate in the conservative fluid management arm is 17.5%, and the rate of extrarenal complications is 7.5%. Detectable absolute differences for these two outcomes with 80% and 90% power, at approximately the same ICC as estimated for the primary outcome, are provided (Table 4). Here, a conservative Bonferroni correction (alpha = 0.025) is used.

**Table 4 Tab4:** Power calculations for secondary outcomes

Outcome	Power	Detectable difference with 20 sites (*n* = 800)	Detectable difference with 26 sites (*n* = 1040)
Hemolytic uremic syndrome—17.5% in conservative fluid management arm	80%	7.2%	6.3%
	90%	8.1%	7.1%
Extrarenal complications—7.5% in conservative fluid management arm	80%	4.7%	4.1%
	90%	5.2%	4.6%

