### Plans to promote participant retention and complete follow-up {18b}

Baseline symptom data will be collected from participants; testing, treatment, and outcome data will be extracted from the medical record. A 30-day (± 7 days) evaluation of renal function is required in the small subset of participants who have an elevated creatinine at the time of pathway termination in children who do not require RRT, to determine the MAKE30 primary outcome. This laboratory evaluation is considered standard of care and thus, no specific research follow-up is required.

A participant will be considered lost to follow-up if a 30-day follow-up serum creatinine value is required to assign MAKE30 status, and none is performed as part of clinical care, or the result cannot be obtained. To minimize lost to follow-up, the following actions will be taken by the clinical care team if a participant fails to return to the clinic for the required follow-up:The clinic will attempt to contact the participant. If contact is made, the clinical care team will counsel the participant on the importance of serum creatinine monitoring. If the participant is unable or unwilling to attend the study site phlebotomy laboratory as directed, the site will provide an alternate, more convenient location for serum creatinine testing.If step 1 is unsuccessful, the research team will make every effort to regain contact with the participant, employing, where possible, up to 3 telephone calls and, if necessary, a certified letter to the participant’s last known mailing address or local equivalent methods. This contact will serve to reinforce the importance of clinical follow-up and we will re-connect the participant with the clinical care team.

Non-adherence with the allocated fluid administration protocol by the clinical care team will not impact research data collection and study procedures; we will collect all primary and secondary outcomes data as well as AEs, SAEs, and unanticipated problems (UP) regardless of adherence status. Participants are free to withdraw from the study at any time thereby terminating further data collection. The reason for participant discontinuation or withdrawal will be recorded.

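### The rule for who needs a day-30 creatinine for MAKE30 is stated two ways, and the two differ for inpatients whose fluid pathway is stopped early without RRT

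*Protocol article*

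**What the plan says.** All references are to the protocol article.

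- **Outcomes, Table 1 (MAKE30).** On the values to be measured at day 30: "these will only be required for participants with an elevated value at the time of fluid pathway termination who do not receive RRT".
- **Plans to promote participant retention and complete follow-up {18b}.** The 30-day evaluation is needed in "participants who have an elevated creatinine at the time of pathway termination in children who do not require RRT". The same section counts a child as "lost to follow-up if a 30-day follow-up serum creatinine value is required to assign MAKE30 status" but no result is available.
- **Participant timeline, Table 2, footnote 8.** The creatinine test applies to "those with elevated creatinine at hospital discharge who do not receive RRT or, if out-patient, at the time of study intervention phase discontinuation".
- **End-of-fluid protocol criteria.** A pathway ends in the ordinary way on platelet, diarrhea and illness-day criteria. It also ends early for a decision to start RRT, anuria of 12 h or more, hypoxemia needing oxygen, weight gain above 15%, or hypertensive emergency. After an early stop "the treatment pathway will not resume once they are resolved", and the responsible physician directs further care.

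**The concern.** Two rules for collecting one component of the primary outcome disagree, and the article does not rank them. Footnote 8 gives inpatients and outpatients different time points, so it does not treat discharge and the end of the intervention as the same moment.

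What is at stake is whether a sustained doubling of creatinine is looked for at all. A site applying Table 1 need not test a child whose creatinine rose only after an early stop; a site applying footnote 8 must. The rule also feeds the loss-to-follow-up count. Read literally, {18b} counts a child as lost only if the value was required, so under the Table 1 rule this child need not appear as missing and would presumably be classed as free of the component. An analysis plan cannot settle this afterwards, because it cannot recover a creatinine that was never drawn.

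**Working it through.** No figure in the article depends on this trigger, so there is none to reproduce. The check is mainly textual, followed by a ceiling on size.

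**Step 1: where the two times coincide.** The ordinary end-of-pathway criteria are the same as the discharge criteria in the Fig. 3 caption, and the Fig. 4 caption applies them to the conservative arm. For ordinary completers, termination and discharge are therefore close together. Outpatients are treated consistently: footnote 8 uses discontinuation of the intervention phase for them.

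**Step 2: where they part.** Of the five early-stop reasons, a decision to start RRT drops out once RRT is given, since the child then already has MAKE30. Anuria, hypoxemia, weight gain above 15% and hypertensive emergency remain. Such an inpatient may stay in hospital with the pathway ended. For such a child without RRT:

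| Creatinine at early stop | Creatinine at discharge | Table 1 and {18b} | Footnote 8 |
|---|---|---|---|
| not elevated | not elevated | not required | not required |
| elevated | elevated | required | required |
| not elevated | elevated | **not required** | **required** |
| elevated | not elevated | **required** | **not required** |

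The rules conflict in the last two rows, in opposite directions. Row three can hide a true event. In row four creatinine has come back to normal, so the main effect is on who is tested and who is counted as lost.

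**Step 3: a ceiling on size.** Inputs:

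- Sample size section: 1040 children, so 520 per arm; conservative-arm HUS 17.5%; conservative-arm MAKE30 about 10%; target difference 5 points.
- Abstract, on children with HUS: "over half of whom require acute dialysis and 3% die".
- Discussion: 60% of children with HUS need RRT.
- Assumption: RRT occurs only in children with HUS.

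Expected HUS cases are 520 × 0.175 = 91. The points of MAKE30 left for sustained loss plus death without RRT are 10 − 17.5 × (share of HUS given RRT):

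- RRT in 50% (the floor of the abstract's range): 10 − 8.75 = 1.25 points; 0.0125 × 520 = 6.5 children.
- The same, if all HUS deaths (91 × 0.03 = 2.73) occurred without RRT: 6.5 − 2.73 = 3.77 children, or 0.73 points.
- RRT in 55% (an intermediate assumption): 10 − 9.625 = 0.375 points; 1.95 children, before removing deaths.
- RRT in 60%: 10 − 10.5 is below zero, so nothing is left.

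The residual in the conservative arm therefore runs from none to about 6.5 children, and the upper end still includes deaths, which are captured anyway. The children at issue are the part of this residual who were stopped early, had normal creatinine at the stop and raised creatinine at discharge, and had no day-30 value from clinical care. The documents do not give that share, or a comparable split for the hyperhydration arm.

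**The case against.** The strongest reply is that standard care closes most of the gap. A row-three child leaves hospital with raised creatinine, and the sample size section expects that "participants with elevated creatinine values at the time of discharge will have laboratory follow-up as part of their standard clinical care". The retention section calls the 30-day evaluation standard of care. The Outcomes section adjudicates MAKE30 on laboratory values and chart documentation as well as 30-day results, and nothing bars using a value that was not required. This stands, and it is the main reason the point is minor.

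Two further replies have force. The loss-to-follow-up definition can be read functionally: a child discharged with raised creatinine and no RRT needs a day-30 value to be classified, whatever Table 1 says. And this is a condensed article: the full protocol and the Manual of Operations are not shown and may fix the working rule. The body of Table 2 is not shown either, and footnote 8 does not itself name day 30, though its restriction to elevated creatinine without RRT makes that reading likely. None of this removes the mismatch in the published text.

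A reader might take the sample size sentence as a further trigger. It is an expectation about standard care and sets no testing rule.

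A reader might also infer a bias toward hyperhydration with an inflated type I error. That arm aims for a 10% weight gain, while in the conservative arm "the target is euvolemia and maintaining weight gain below" 5%, so stops for gain above 15% could be commoner under hyperhydration. The documents do not carry this further. The other stop reasons are not clearly tied to one arm, and no share of missed events is given for either. A type I error figure would require inventing that share, applying it to a ceiling that includes deaths captured anyway, and placing all of it in one arm.

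**Conclusion.** The inconsistency is real: Table 1 and {18b} on one side, footnote 8 on the other, with no statement of which governs. It affects only inpatients stopped early without RRT whose creatinine status changes between the stop and discharge. Their number is unknown and probably very small. The ceiling of about 6.5 conservative-arm children (1.25 points, against a 5-point target) rests on the planning rates, on RRT in only half of HUS cases and on RRT occurring only in HUS; it falls to none at 60% RRT. The affected group is some unstated fraction of it. Neither a type I error figure nor a firm direction of bias is supported. Severity: minor.

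**What to change.** Use one trigger, worded identically for both arms, in Table 1, in footnote 8 to Table 2 and in {18b}: in a child without RRT, creatinine elevated at pathway termination **or** at hospital discharge (for outpatients, at discontinuation of the intervention phase). Either time should suffice. A rule based on the later time alone would drop children elevated at the stop but normal at discharge, whom Table 1 and {18b} now require to be tested. The sample size section needs no change.

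State also that any creatinine from clinical care at day 30 ± 7 is used whether or not it was required, and report by arm the numbers flagged, tested and missing.

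The cost is a few extra day-30 draws, none beyond what one of the two present rules already asks for, and a short amendment to the IRB/REBs while recruitment runs (planned to September 2026). If the full protocol or the Manual of Operations already fixes the rule, aligning the wording with the either-time trigger is enough.
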